### Data collection

Table 2 displays the schematic diagram for the timeline of patient assessment and data collection. Assessment on surgical safety and postoperative rehabilitation status will be performed by research physicians and recorded by the research nurse within 30-days after the gastrectomy. The case manager will collect demographic information at baseline, conduct life quality assessment one-year postoperative, and do follow-up on survival status till three-years after the last treatment. After gathering all relevant data collected by physicians, research nurse, case manager, as well as lab tests and imageological examinations, the data manager is responsible for data storage, security, management, and quality control. Data quality will be double-checked by the research physician aperiodically to further promote data accuracy and completeness.

**Table 2 Tab2:** Schematic diagram for the schedule of enrolment, interventions, and assessments

TIMEPOINT	STUDY PERIOD						
	Enrolment	Allocation	Post-allocation				Close-out
	*-2 to − 4 weeks*	0	*1 week*	*4 weeks*	*Year 1* ^a^	*Year 2* ^a^	*Year 3* ^b^
ENROLMENT:							
Eligibility screen	X						
Informed consent	X						
Allocation		X					
INTERVENTIONS:							
*Open gastrectomy*			X				
*Laparoscopic gastrectomy*			X				
ASSESSMENTS:							
*Physical examination*	X				X	X	X
*Laboratory tests*	X				X	X	X
*Oncology assessment*	X				X^c^	X^c^	X^c^
*Geriatric assessment*	X						
*Surgical safety*				X			
*Postoperative rehabilitation*				X			
*Life quality*					X^d^		
*Survival status*					X	X	X

^a^conducted on a 3-month basis

^b^conducted on a 6-month basis

^c^conducted if recurrence is suspected

^d^conducted at the end of Year 1

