### Study design, setting, and participant

This is a prospective, randomized, single-center, open-label phase II trial, which takes place in the Gastrointestinal Cancer Center of Peking University Cancer Hospital and Institute, China (Fig. 1). Adult ambulatory patients aged 70 and above, with Karnofsky Performance Status (KPS) ≥ 70, histology proved gastric cancer, cT2-4aNanyM0 (UICC TNM staging 7th edition), and no prior cancer treatment, will be screened for inclusion and exclusion criteria (Table 1) by the reception oncologist. Eligible patients will be invited for study participation at their first visit at the Gastrointestinal Cancer Center. The doctor who sees the patient will give a formal and detailed description of the study and its procedures. Upon the acquisition of patient written informed consent form, patients will undergo oncology evaluation (e.g. abdominal enhanced CT and/or MRI scan, chest plain scan CT, cervical lymph node, ultrasonography, pelvic ultrasonography/CT, serum tumor markers, laparoscopic exploration and free cytological examination of peritoneal cavity) as well as geriatric assessment with G8 screening tool. Patients will afterwards be randomized 1:1 to either laparoscopic or open surgery arm by the data manager in the team using random number table. None of patients, surgeons, or data analysts will be blinded.

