### Assessment of outcomes

#### Primary endpoints

The primary endpoint is surgical safety, including complication rate, reoperation rate, readmission rate, and mortality rate within 30 days after surgery. Surgery related complications include incision complications (infection, effusion, dehiscence, poor healing), peritoneal effusion or abscess formation, hemorrhage (inside abdominal cavity, inside digestive tract), ileus, anastomotic leakage, anastomotic stenosis, intestinal fistula, lymphatic leakage, pancreatic fistula, gastroparesis, pancreatitis, lung infection, pleural effusion, urinary tract infection, renal failure, liver failure, cardio-cerebrovascular events (both lower extremities thrombosis, pulmonary embolism, myocardial infarction, arrhythmia, cerebral infarction, etc.), and others. Complications will be reported and graded according to the Clavien-Dindo classification of surgical complications.

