**Roles and responsibilities**

***Principal investigator and research physicians***

Design and conduct of the trial

Preparation of protocol and revisions

Preparation of case report forms

Preparation of materials for international review, board/independent ethics committee applications

Patient enrolment

Performing surgery

Publication of study reports

Members of Trial Management Committee

Annual progress reporting to the funder and ethics committee

Serious adverse events reporting to ethics committee

Responsible for trial data file

Budget administration

Data verification

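### The role that performs the operations also assesses and double-checks the open-label primary outcome, and no rule keeps surgeons from judging their own cases, so differential recording could materially inflate the false-positive rate

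*Protocol article*

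**What the plan says.** Under Data collection, the protocol article gives the primary outcome to one group: "Assessment on surgical safety and postoperative rehabilitation status will be performed by research physicians", with the result "recorded by the research nurse within 30-days after the gastrectomy". The same section adds a check by that group: "Data quality will be double-checked by the research physician aperiodically". It makes the data manager responsible for quality control.

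The roles list has one joint heading, "Principal investigator and research physicians". Among the duties under it are "Performing surgery" and "Data verification". Data verification is also listed for the data manager, who randomizes the patients.

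On blinding, Study design, setting, and participant says: "None of patients, surgeons, or data analysts will be blinded". Outcome assessors are not named there.

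Primary endpoints lists the complications that count. Some are hard events (anastomotic leakage, haemorrhage, myocardial infarction). Others leave room for judgement (incision effusion, poor healing, peritoneal effusion, pleural effusion, and an open category of others). On grading it says: "Complications will be reported and graded according to the Clavien-Dindo classification of surgical complications". Neither that section nor Statistical analysis says which grades enter the complication rate that is powered and tested.

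The funding agency monitors and audits once a year (Data monitoring, auditing, and interim analysis).

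**The concern.** Surgery of this kind cannot be blinded to the surgeon. It is avoidable, however, that the operator decides whether his or her own patient had a complication. The article assigns operating, assessing and verifying to one role and states no separation within it. The trial's stated hypothesis is that laparoscopy is safer.

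If a borderline effusion or slow-healing wound is recorded less readily in one arm, the recorded complication rate in that arm falls directly. Intention-to-treat analysis does not correct this, because the patient stays in the right arm with the wrong outcome. Multiple imputation does not either, because the outcome is not missing. At stake is the meaning of a significant difference in the one rate on which the trial is powered.

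**Working it through.** **1. The assignment of duties, side by side**

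| Step | Who does it | Where stated | Independent of the operation, or masked? |
|---|---|---|---|
| Operating | Two experienced surgeons; duty listed under principal investigator and research physicians | Interventions; roles list | – |
| Assessing surgical safety | Research physicians | Data collection | Not required |
| Recording | Research nurse | Data collection | Records the assessment; adjudication not described |
| Double-check | Research physician, at irregular intervals | Data collection | Not required |
| Quality control, verification | Data manager, who also randomizes | Data collection; roles list | Knows the allocation |
| Audit | Funding agency, annually | Data monitoring section | No review of complications described |

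No row supplies a judgement of the outcome that is separate from the operator or masked to arm.

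**2. The plan's own sample size**

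Inputs from Statistical analysis: 35% in the open arm, a decrease of 19 read as percentage points (so 16%), two-sided 0.05, 80% power. With pooled variance and no continuity correction:

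n = [1.960·√(2·0.255·0.745) + 0.842·√(0.35·0.65 + 0.16·0.84)]² / 0.19²
= (1.208 + 0.506)² / 0.0361 ≈ 81.4, so 82 per arm.

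This matches the stated 164, so 35% and the uncorrected chi-squared test are a fair basis for the next step.

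**3. Effect of differential recording**

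Assume no true difference: 35% in both arms. Let u be the fraction of affected laparoscopic patients recorded as having no complication. The recorded laparoscopic rate is then 0.35·(1 − u). The chance of a significant result favouring laparoscopy is the sum of the binomial probabilities over all pairs of counts for which the pooled two-proportion z exceeds 1.96 in that direction.

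| u (assumed) | Recorded laparoscopic rate | 90 per arm | 82 per arm |
|---|---|---|---|
| 0 | 35% | 2.6% | 2.5% |
| 10% | 31.5% | 7.2% | 6.9% |
| 15% | 29.8% | 11.3% | 10.7% |
| 20% | 28% | 17.0% | 16.0% |
| 30% | 24.5% | 33.7% | 31.3% |
| 40% | 21% | 55.6% | 51.7% |

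If the true rate is 25% in both arms, the figures at 90 per arm are 2.5%, 5.8%, 8.5% and 12.1% for u of 0, 10%, 15% and 20%.

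**4. How much loss would produce significance in a typical trial**

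With 31/90 affected in the open arm (34.4%), significance needs at most 19/90 in the laparoscopic arm by chi-squared (p = 0.046), or 18/90 by Fisher's exact test (p = 0.044). Starting from equal true counts, 12 or 13 of 31 affected laparoscopic patients would have to go unrecorded: 12/31 = 39%, 13/31 = 42%.

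**5. If only minor events are at risk**

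The article gives no split by severity. Suppose 50% to 70% of affected patients have minor events only (an assumption). At 90 per arm, missing 20% of those gives a false-positive chance of 7% to 10%; missing half gives 25% to 44%.

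**6. If there is a small true benefit**

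With true rates of 35% and 27% and 90 per arm, the chance of significance is 21% with complete recording, 35% at u = 10% and 52% at u = 20%.

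**The case against.** The strongest reply is that the roles list pools the duties of a team, budget administration and enrolment among them. It does not say that every member does everything. Operating is confined to two surgeons, while assessment falls to research physicians in general. A nurse records, laboratory and imaging results feed in, the data manager verifies as well, and the funder audits. Reoperation, readmission and mortality are also primary measures and are harder to under-record. The Discussion sets out the harms of pneumoperitoneum and calls the benefit controversial, so one-sided belief cannot be presumed.

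Much of this stands, and it rules out some stronger readings that a reader might infer:

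- **That the same individual operates and assesses.** The text shows a shared role, not a shared person. That assessors know the arm is also inferred from the role, because the blinding statement does not name them.
- **That every Clavien-Dindo grade counts.** No threshold is stated, but silence in a condensed article is not a rule that all grades count.
- **That modest under-recording would by itself create the superiority result.** With no true difference, a 20% loss still leaves 83% of trials without a false result favouring laparoscopy.

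The reply does not supply the missing separation. The nurse records what the physicians assess, the data manager knows the allocation, and an annual audit is not case-by-case adjudication. The overlap of duties is something the article states, not something it merely leaves out.

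**Conclusion.** The point holds as a weakness in how the primary outcome is ascertained. The role that operates also assesses and double-checks surgical safety in an open-label trial, and no stated step gives an operator-independent or masked judgement.

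The plausible harm is a materially inflated false-positive rate, roughly three-fold at 10% differential loss (7.2/2.6) and between six- and seven-fold at 20% (17.0/2.6). A small true benefit could also be pushed to significance. These sizes rest on three assumptions: a true rate of 35%, loss in the laparoscopic arm only, and the chosen loss fractions. The documents support neither the direction nor the amount of loss. The article does not show that bias will occur. It shows that the plan lacks a cheap protection against it.

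**What to change.** Amend Data collection so that each patient's 30-day complications are adjudicated, graded and verified by an existing research physician who took no part in that patient's operation. That physician should work from the nurse-recorded case report form and the laboratory and imaging results, with the surgical approach removed where feasible. Masking will be incomplete, because incision complications are themselves counted.

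The cost is protocol wording and a small reassignment of duties within the team. The sample size does not change.

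A grade II floor for the primary rate is not recommended here. It would redefine the powered endpoint, and the grades behind the 35% are not given; if that figure counts all grades, a floor would lower the control rate and undo the 82 per arm. At most, Primary endpoints should state which Clavien-Dindo grades the rate counts, and Statistical analysis should confirm that the 35% uses the same definition.

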**Methods:**

The current study has a randomized, parallel controlled, single-center, open-label, superiority design with two arms. A sample of 180 local advanced gastric cancer patients aged 70 and above will be recruited in Peking University Cancer Hospital and Institute. Participants will be randomized to either receive open or laparoscopic gastrectomy. The primary outcome is surgical safety, including complication rate, reoperation rate, readmission rate, and mortality rate within 30 days after surgery. The secondary endpoints include postoperative rehabilitation status, one-year postoperative life quality, three-year overall and disease-free survival. Assessments will take place at baseline (before random assignment), at 30 days, one-year, and three-year after the surgery. The study has been approved by an ethical review board.

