### Interventions

All patients will receive surgery within one week after randomization. Perioperative enteral/parenteral nutrition support will be allowed for patients with nutritional risk. The patients will be fasted of food and water 1 day and 4 h before the surgery, respectively. Patients will not normally receive preoperative gastrointestinal decompression, except for those with digestive tract obstruction. Prophylactic use of antibiotics during the perioperative period will be in accordance with relevant national regulations. All patients with pathology proved advanced gastric cancer will be suggested to use adjuvant chemotherapy, the regimen of which will be in line with the Japanese Gastric Cancer Treatment Guideline (version 5th) [11].

A standard laparoscopic or open radical gastrectomy will be performed by two experienced surgeons for all enrolled patients. In the open group, an approximately 20- to 25-cm incision will be made from the falciform process to the periumbilical area [12]. In the laparoscopic group, one 10-mm trocar for the camera will be inserted below the umbilicus [12]. Another three 10-mm ports will be inserted in the left upper quadrants 2 cm below left lower rib margins, the right and left flank areas, respectively [12]. One 5-mm trocar will be lastly placed at the right upper quadrants 2 cm below right lower rib margins [12]. Pneumoperitoneum will be achieved using carbon dioxide with a pressure maintained at 8-12 mmHg. Greater omentum resection, lymph node dissection, and vascular treatment will be performed under laparoscopy. Gastrectomy and digestive tract reconstruction may be performed by the surgeon under laparoscopy or assisted incision, as appropriate. All abdominal operation of laparoscopy will be videotaped. Anastomosis will be performed using the instrumental method. The specimen will be pulled out through a small median incision under the xiphoid (about 3–8 cm). In both groups, the range of gastric resection and lymph nodes dissections will be done in accordance with the Japanese Gastric Cancer Treatment Guideline (version 5th) [11]. Surgeons will decide the digestive tract reconstruction approach according to the intraoperative circumstances. Considering the healing capacity of elderly patients, local drainage will be placed on both sides of the anastomotic stoma.

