### Patient follow-up

Information on prognostic status is collected via follow-up till 3 years after the last treatment. Follow-up will be conducted on a 3-month basis in the first two years and every half-year in the third year. In each follow-up, participants receive physical examinations (i.e. height, weight, KPS, routine examination of heart/lung/abdomen), laboratory tests (including blood cell test, blood biochemical test, and serum tumor marker test), imageological examinations (including ultrasonography [every 3 months], enhanced CT/MRI [every 6 months], endoscopy [every 12 months], and chest radiograph). Tumor assessment will be conducted if recurrence is suspected, and further treatment such as surgery or chemotherapy will be administered when needed and will be recorded in the case report form. To promote participant retention and complete follow-up, three attempts will be made to contact and remind the participants to come to the hospital for follow-up, and their transportation fee will be covered by the research project.

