### Adverse events

Adverse events are any unfavourable or unintended events that affect patients on study, regardless of the relevance to the treatment [16]. Any adverse events will be recorded in detail on the CRF regarding its occurrence time, duration, relevance to the treatment, stopping or continuing of the treatment, etc. [16]. Events are defined as serious adverse events if leading to death, prolongation of hospitalization, permanent or severe disability, teratogenesis or carcinagensis, and significant clinical sequela [16]. The occurrence of serious adverse events will be reported to Peking University Cancer Hospital Ethics Committee within 24 h of the initial discovery [16].

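### The primary-endpoint assessment has three inconsistent timings, and the one in Table 2 falls 2 to 9 days before the 30-day window closes

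*Protocol article*

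**What the plan says.** The Primary endpoints section defines surgical safety as "complication rate, reoperation rate, readmission rate, and mortality rate within 30 days after surgery", and the Statistical analysis section compares 30-day rates. The clock for the endpoint therefore starts at surgery and runs for 30 days.

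Three places say when the assessment is made:

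- **Abstract, Methods:** "Assessments will take place at baseline (before random assignment), at 30 days, one-year, and three-year after the surgery".
- **Data collection, text:** safety and rehabilitation assessment is "performed by research physicians and recorded by the research nurse within 30-days after the gastrectomy".
- **Data collection, Table 2:** allocation is time 0, gastrectomy is in the 1-week column, and the single mark for surgical safety (and for postoperative rehabilitation) is in the 4-week column. All of these columns after time 0 stand under a post-allocation heading.

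The Interventions section links the two clocks: "All patients will receive surgery within one week after randomization". After the 4-week column, the next contacts are those in Patient follow-up: "Follow-up will be conducted on a 3-month basis in the first two years". Table 2 has no surgical-safety mark at those visits.

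**The concern.** The abstract and the Data collection text count from surgery, whereas Table 2 counts from allocation. A team working from the table would make the only scheduled safety assessment before any patient had completed 30 postoperative days. The period covered would also vary between patients with the wait for surgery.

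The events most exposed are those after discharge: readmission, reoperation, and complications that appear late or are treated elsewhere. If nobody asked about them later, rates covering 21 to 28 days would be reported as 30-day rates. The trial is open-label, with patients, surgeons and analysts all unblinded, so ascertainment of the primary endpoint needs to be uniform and tied to the date of surgery.

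**Working it through.** **Inputs from the protocol article**

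- Endpoint window: 30 days from surgery (Primary endpoints).
- Day of surgery, counted from allocation: s = 0 to 7 (Interventions).
- Table 2 safety visit: 4 weeks after allocation, taken as day 28.
- Planning values: 35% in the open arm and a 19-point reduction, so 16% in the laparoscopic arm; two-sided 0.05; 80% power; 82 per arm (Statistical analysis).

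**Step 1. Calendar**

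Postoperative day of the visit = 28 − s. Days of the window still to run = 30 − (28 − s) = 2 + s.

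| Surgery on day s | Postoperative day of visit | Days of window remaining |
|---|---|---|
| 0 | 28 | 2 |
| 3 | 25 | 5 |
| 7 | 21 | 9 |

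So 2/30 = 7% to 9/30 = 30% of the window lies after the visit. Table 2's own placement of surgery at 1 week corresponds to the last row. To close the window, a visit counted from allocation would have to fall on day 30 + s, that is day 30 to 37.

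**Step 2. The plan's sample size**

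For two proportions with pooled variance under the null and no continuity correction:

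n per arm = [1.96·√(2·p̄·(1−p̄)) + 0.8416·√(p₁(1−p₁) + p₂(1−p₂))]² / (p₁−p₂)²

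With p₁ = 0.35, p₂ = 0.16 and p̄ = 0.255:

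- first term: 1.96 × √0.37995 = 1.208
- second term: 0.8416 × √0.3619 = 0.506
- n = (1.714)² / 0.0361 = 81.4, rounded up to 82

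This reproduces the stated 82 per arm. Power at 82 per arm is Φ[(0.19·√82 − 1.208)/0.6016] = Φ(0.852) = 80.3%. The timing issue does not alter this calculation.

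**Step 3. Illustration of what unrecorded events would cost**

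The article gives no share of complications arising after postoperative day 21 to 28. Assume that a fraction f of patients with a complication, the same in both arms, have it only after the visit and that it is never recorded. The observed rates become 0.35(1−f) and 0.16(1−f). The same power formula at 82 per arm gives:

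| f (assumed) | Observed rates | Power |
|---|---|---|
| 0 | 35.0% v 16.0% | 80.3% |
| 2% | 34.3% v 15.7% | 79.2% |
| 5% | 33.25% v 15.2% | 77.5% |
| 10% | 31.5% v 14.4% | 74.5% |

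**Step 4. Other routes by which an event could be found**

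- *Deaths:* overall survival runs from gastrectomy to death from any cause, and survival status is followed every 3 months in the first two years. A death between the visit and day 30 would be found and dated.
- *Adverse events:* "Any adverse events will be recorded in detail on the CRF regarding its occurrence time, duration", with no 4-week cut-off. A known event can therefore be placed inside or outside the 30 days. The section schedules no contact to discover events after discharge, and its definition of a serious event names prolonged hospitalisation but not readmission.
- *3-monthly visits:* the listed content is examination, laboratory tests and imaging. No look-back question on complications, readmission or reoperation is listed.

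**The case against.** The strongest reply is that the article already gives the right time. The abstract states 30 days after surgery. The Data collection sentence counts from gastrectomy, and its wording resembles the endpoint definition, where it plainly means through day 30. The natural reading is a recording period, not one early visit. Table 2 is introduced as a "schematic diagram" in substance: its Year 1 column stands for several visits and its 1-week column for surgery on any day of that week, so reading 4 weeks as exactly day 28 is the least favourable choice.

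Much of this stands. A reader might infer that the Data collection text repeats the table's fault, that ascertainment closes early, and that late events, deaths included, are lost. The documents do not support that. The text conflicts with the table and does not repeat its timing; deaths are caught by survival follow-up; and known adverse events carry dates. Nor does anything say that recording of hospital stay or drain removal stops at the 4-week visit, or that the wait for surgery differs by arm, since the one-week limit applies to everyone.

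What remains is that a recording period through day 30 does not itself fix a contact on or after day 30. Only the abstract does so, and neither the Data collection text nor the schedule repeats it. The table is also presented as the timeline for assessment and data collection, and it is the only schedule in the article.

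**Conclusion.** The point holds as an internal inconsistency in the timing of the primary-endpoint assessment, of minor to moderate severity. Taken literally, Table 2 places the only scheduled safety assessment on postoperative day 21 to 28, which is 2 to 9 days before the window closes. Late complications, readmissions and reoperations after discharge can then be missed; deaths should not be.

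The calendar result rests only on the article's own figures and on reading 4 weeks as day 28. The power figures rest on an assumed late-event share and on those events never being recorded by any route. They show sensitivity and are not an estimate of harm. The planned 82 per arm is unaffected.

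**What to change.** Relabel the 4-week column of Table 2 as 30 days after surgery, counted from the date of gastrectomy, with the visit not before day 30. Reword the Data collection sentence to say that surgical safety is assessed on or after day 30 for all events in days 0 to 30, in the same way in both arms. The table and text then agree with the abstract, the endpoint definition and the 30-day rates in the Statistical analysis section.

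The cost is one column label and one sentence. Relative to a literal reading of Table 2, the contact moves 2 to 9 days later. No extra patients are needed and no sample-size figure changes.
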